## Abstract

**Background:**

*BRCA *mutation carriers have a 40-80% life-time risk of developing breast cancer. They may opt for yearly breast cancer surveillance or for prophylactic mastectomy. Both options show increased survival rates. It is a complex choice to be made between these two options. As a result most women experience high levels of distress and high needs for information. To fulfill the needs for psychosocial support and information we have introduced group medical consultations (GMCs). A GMC provides individual medical visits conducted within a group. This 90 minute group-visit with 8-12 patients gives patients the opportunity to spend more time with their clinician and a behavioral health professional and learn from other patients experiencing similar topics. However, it should be noted that group sessions may increase fear in some patients or influence their decision making.

**Methods/design:**

In this randomized controlled trial, 160 BRCA mutation carriers diagnosed maximally 2 years ago are recruited from the Radboud University Nijmegen Medical Centre. Participants are randomized in a 1:1 ratio to either the GMC intervention group (onetime participation in a GMC instead of a standard individual visit) or to a usual care control group. Primary outcome measures are empowerment and psychological distress (SCL 90). Secondary outcome measures are fear of cancer, information needs before the consultation and the received information, self-examination of the breasts, patient satisfaction, quality of life and cost-effectiveness. Data are collected via self-reported questionnaires 1 week before the visit, and at 1 week and at 3 months follow-up. A pilot study was conducted to test all procedures and questionnaires.

**Discussion:**

The possibility for interaction with other BRCA mutation carriers within a medical visit is unique. This study will assess the effectiveness of GMCs for BRCA mutation carriers to improve empowerment and decrease distress compared to individual visits. If GMCs prove to be effective and efficient, implementation of GMCs in regular care for BRCA mutation carriers will be recommended.

**Trial registration:**

The study is registered at ClinicalTrials.gov (NCT01329068)

## Background

*BRCA *mutation carriers have a high life-time risk of developing breast cancer and also of ovarian cancer. In a large meta-analysis of ten studies the mean cumulative breast cancer risk at 70 years was 46-80% for *BRCA1 *mutation carriers and 40-80% for *BRCA2 *mutation carriers [1-3]. Because of this high risk of breast cancer, women with a mutation in either the *BRCA1 *or *BRCA2 *gene are offered breast cancer surveillance, which includes annual clinical breast examination, annual mammography and annual contrast enhanced magnetic resonance imaging (MRI) of the breast [4-6]. Alternatively, women may opt for prophylactic bilateral mastectomy with or without breast reconstruction [7-10]. Prophylactic bilateral mastectomy reduces the risk for breast cancer by 89.5-100%[11], making yearly surveillance unnecessary. Although prophylactic mastectomy minimizes the risk of breast cancer, comparable survival rates are seen for prophylactic mastectomy and yearly breast cancer surveillance [10].

*BRCA *mutation carriers who underwent treatment for breast cancer before, have to deal with a 50-64% lifetime risk for developing a second primary breast cancer [12]. Most studies among *BRCA *mutation carriers who had breast cancer have shown a reduction in the risk of contralateral breast cancer, while results on survival rates were diverse [10,13-15]. Besides, the decision for contralateral prophylactic mastectomy depends on age, type of initial breast cancer surgery, prophylactic oophorectomy and the patient's opinion [16].

Thus, *BRCA *mutation carriers face a complex choice between these options. The knowledge of *BRCA *carriership and the consequently increased risk of developing breast (and ovarian) cancer may have a large psychosocial impact on mutation carriers. The level of cancer related distress among Jewish women increased significantly after the diagnosis of a *BRCA *mutation [17]. In another study 36 percent of women diagnosed with a *BRCA1 *mutation appeared to be sad or crying [18]. Several studies in the Netherlands showed that genetic testing, regardless of the test results may already increase levels of distress [19,20].

The provision of psychosocial support is intrinsically connected to the provision of guidance in the choice between surveillance and a prophylactic mastectomy. In a study of 233 women who were awaiting their initial appointments for risk assessment, consideration of prophylactic mastectomy strongly correlated with high levels of breast cancer anxiety and overestimation of one's breast cancer risk, whereas there was no association with objective breast cancer risk [21]. Recently, it was suggested that standard visit with a psychologist for high-risk women considering prophylactic mastectomy may be indicated since anxiety is one of the main reasons for considering a prophylactic mastectomy, and depression and grief were present in a third of the participating women [22]. Interestingly, in this study uncertainty about surgery and the need for further information were the reasons given most frequently for postponing prophylactic mastectomy, indicating that there is a great need for information in this group [23]. Generally, the decision about surveillance or prophylactic mastectomy is not a medically urgent one and women can indeed take time to gather and process all information and talk about it with others. Of note, patient satisfaction is an important predictor of quality of life, treatment compliance and lower rates of anxiety and depression [24]. In previous studies it has been shown that in order to improve the patient satisfaction it is important for the clinician to discuss psychosocial factors and to be responsive to the patients concerns [25,26].

To fulfill the needs just mentioned concerning psychosocial support and information we have introduced group medical consultations (GMCs) for the surveillance of *BRCA *mutation carriers. A GMC provides individual medical visits conducted within a group, giving patients the opportunity to spend more time with their own clinician in the setting of a support group with a behavioral health professional and learn from other patients experiencing similar topics. In contrast to the typical 15-20-minute office visit, a 90-minute group-visit with 8-12 patients permits ample time for discussion and education. The incorporation of the individual medical visit in a GMC distinguishes GMCs from educational workshops and support- and self-management groups. In general, the group of patients in a GMC is composed of different participants from meeting to meeting. Currently, GMCs have been offered to patients of different ages with a variety of diseases [27,28]. Although several benefits of GMCs compared to individual visits have been reported, the effects have not been evaluated for the surveillance of *BRCA *mutation carriers.

Most previous studies showed improved satisfaction in patients receiving GMCs and in health professionals providing GMCs. The unhurriedness of the clinician and the time spent with the clinician is appreciated most by patients [29-33]. Clinicians were positive about the innovative and multidisciplinary working method [34]. Besides improved quality of life, which is reported in several studies [32,35,36], also improved health behavior, self-efficacy for following certain health promoting interventions and knowledge of the disease was shown among diabetes patients and patients with coronary artery disease who participated in a group visit [35,37]. Also, quality of care is improved. For example, in a study of diabetic patients group visit participation was positively associated with patients receiving preventive procedures, review of medication and microalbuminuria test recorded in the registry [38]. Other studies in diabetic patients have confirmed these results [31,39-41]. When planned carefully, this type of visits may increase clinician satisfaction and productivity [30,36,42-44].

However, it should be noted that group sessions may not be beneficial [45]. Recently the effects of educational-support groups for *BRCA *mutation carriers have been studied [46]. This program included eight sessions with alternately a psychosocial (5 sessions) and a medical information focus (3 sessions); no individual visits were provided in the group. The study provided presumptive evidence that educational-support group participants were more inclined to undergo prophylactic mastectomy than non-participants. Possibly the occurrence of group members getting cancer during surveillance affected other group members. Group participation may have triggered feelings of anticipated regret, i.e. regret that women think they would have if they were to be diagnosed with breast cancer after not (yet) having chosen the option of prophylactic mastectomy [47]. Therefore, before introducing GMCs in regular patient care for *BRCA *mutation carriers the pros and cons of GMCs for this population should carefully be evaluated.

## Methods/Design

### Design

The study examines the effect of GMCs on patient empowerment and psychological distress of *BRCA *mutation carriers as well as several secondary outcome measures. This randomized controlled trial (RCT) will compare two groups; the intervention group, who will participate in a GMC once and the control group, who will receive care as usual (surveillance in an individual visit).

### Ethical consideration

The study has been approved by the medical ethical committee of the Radboud University Nijmegen Medical Centre. Full medical ethical approval has been obtained in February 2011.

### Study sample

A total of 160 recently diagnosed *BRCA *mutation carriers will be invited to participate in the study. To stimulate interaction and discussion within the group it is important to compose heterogeneous groups. Nevertheless, some homogeneity is needed to keep the GMCs relevant for everyone [34]. Therefore the following in- and exclusion criteria were formulated. Inclusion criteria are: carrier of a *BRCA1 *or a *BRCA2 *mutation; diagnosed maximally 2 years ago; and a minimum age of 25. Exclusion criteria are: currently involved in a diagnostic work-up because of a suspicion of breast cancer, either primary or metastatic; a history of prophylactic mastectomy or current psychiatric disease precluding visits in a group; insufficient command of the Dutch language to be able to follow a group discussion and fill out questionnaires in Dutch.

### Recruitment and randomization

Women with the *BRCA *mutation having their yearly surveillance in the Radboud University Nijmegen Medical Centre will be informed about the study during an individual visit to the outpatient clinic or approached via a telephone call by the researcher. As shown in Figure 1 patients will be randomized for their next visit to either the intervention group (GMC) or the control group (individual visit) after informed consent is obtained. Randomization will take place per patient in a 1:1 ration and in blocks of 16 patients. The individual clinician, will meet the same number of patients in a GMC and in an individual consultation, therefore we pre-stratified for clinician.

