The researcher will be present during the GMC for measuring the time spend per patient. This measure will be used in the analyses to test the relation between time spend per patient and the effectiveness of the GMC. Besides, topics discussed during the visits will be measured by the researcher.

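### One published block size of 16 within clinician makes some allocations predictable if women are randomised one by one; allocating each block as a batch would remove this cheaply

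*Protocol article*

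**What the plan says.** The Protocol article, Recruitment and randomization, gives the rule: "Randomization will take place per patient in a 1:1 ration and in blocks of 16 patients". Allocation is for the next visit, "after informed consent is obtained". The same section explains that each clinician is to see equal numbers in both arms, and "therefore we pre-stratified for clinician". The number of clinicians is not given.

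On approach, women are "informed about the study during an individual visit to the outpatient clinic or approached via a telephone call by the researcher". Under Secondary outcome measures, "The researcher will be present during the GMC for measuring the time spend per patient".

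The Abstract describes the intervention as follows: "This 90 minute group-visit with 8-12 patients". With 1:1 allocation, a block of 16 holds 8 GMC places, the lower end of that range. The Abstract also says that outcome data come from self-reported questionnaires, which covers both primary outcomes (empowerment and SCL-90).

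**The concern.** A permuted block of known length has to balance by its end. Once 8 women in a clinician's block have gone to one arm, all the rest go to the other, and the last place in every block is known beforehand. Here the length is one fixed number, printed in the article. The arms are visible to patient, clinician and researcher. The clinician sees both arms of their own stratum, so past allocations can be counted. Hiding the list does not prevent this inference, because it uses only past allocations and the block length.

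Someone who can foresee the next arm might, without intending to, delay approaching an anxious woman or present the study differently. Anxiety and reluctance about groups bear directly on distress and empowerment scores. Adjustment for baseline SCL-90 would remove only the part of such selection that the score captures. What remained would be reported as an effect of the GMC.

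**Working it through.** **Inputs from the Protocol article.** Block size 16, so m = 8 per arm; 1:1 ratio; strata by clinician (Recruitment and randomization). Total 160, hence 160/16 = 10 blocks if all fill (Study sample). SD 45, target difference 13.5, 80 per group with 15% drop-out, so 80 × 0.85 = 68 evaluable per group (Power calculations). The article gives no figure for predictability, so there is none to reproduce.

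**Assumptions.** Women are allocated singly, and an observer knows the running count in each clinician's block.

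**Step 1: allocations known with certainty.** The expected number per block is 2m/(m+1) = 16/9 = 1.78, or 1.78/16 = 11.1%. Over 10 full blocks this is 17.8 of 160 women. The probability that the last k or more are determined is 2·C(16−k, 8)/C(16, 8):
- k = 2: 2 × 3003/12870 = 0.467
- k = 3: 2 × 1287/12870 = 0.20

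**Step 2: best guessing.** If the observer always names the arm that is behind, the expected number of correct guesses is 8 + (2^16/C(16, 8) − 1)/2 = 8 + (5.092 − 1)/2 = 10.05 of 16. That is 62.8%, against 50% by chance.

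**Step 3: possible bias if only certain allocations are steered.** Suppose women at certain places differ in expected SCL-90 by d SD, in opposite directions for the two arms (d is assumed; the article gives nothing). The certain share is 1/9, so bias = 2 × d × 45 × 1/9:
- d = 0.1: 1.0 point (1.0/13.5 = 7% of the target)
- d = 0.25: 2.5 points (2.5/13.5 = 19%)

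With 68 per group and no allowance for baseline correlation, SE = 45 × √(2/68) = 7.72. The two-sided 5% error becomes about 5.2% and 6.2%.

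**Step 4: outer limit.** If every guess were acted on, the factor 1/9 becomes 2 × 0.628 − 1 = 0.256. The bias is then 2 × d × 45 × 0.256 = 2.3 points (d = 0.1) to 5.8 points (d = 0.25), with type I error of about 6% to 12%.

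**Step 5: the alternatives.**
- *Other fixed lengths.* A fixed block of 8 gives 2/(4+1) × 4 = 1.6 certain of 8 (20%). A block of 4 gives 1.33 of 4 (33%). Shortening the block would make matters worse.
- *Random blocks of 16, 20 and 24, equally likely.* Take an observer who knows these sizes and where each block starts, but not the current size. Certainty arises only when one arm reaches 12, that is, in blocks of 24: (1/3) × (24/13)/20 = 3.1% with full blocks, and 2.8% in simulation with 160 women. An observer who does not know where blocks start is certain about 1% of the time. Correct guessing falls only to about 61%.
- *Batch allocation after consent.* No place is allocated while a woman is still being approached, so nothing can be foreseen at consent.

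**The case against.** **Single allocation is not stated.** In a trial of group visits, randomising per patient may simply mean that the woman, not the group, is the unit. Sixteen consented women of one clinician, split 8 and 8 to form one GMC, would fit the same sentence, and predictability would then vanish. This stands. A reader might infer that the article prescribes one-at-a-time allocation; it only suggests it, and the flow chart is not shown.

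**Concealment may be described elsewhere.** Who holds the list and who discloses the arm is commonly left to a full protocol. This stands too: the silence is no defect. The point rests on the fixed, printed block size, which permits inference from past allocations even when the list is well guarded.

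**The researcher's presence at GMCs proves little.** A reader might infer that the person who telephones women learns the sequence by attending. Attendance shows the arm only after allocation, and a GMC of 8 drawn from one block would already have used up that block's GMC places. A usable tally would come mainly from scheduling or from the clinician's own list.

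**The larger bias figures are assumed.** The 2.3 to 5.8 points and 6% to 12% type I error require every guess to be acted on, consistently in one direction, and ignore the planned adjustment for baseline SCL-90. They are an outer limit, not an expected size. Even the smaller figures assume that every certain allocation is used.

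**Sixteen is already a long block.** About 89% of allocations are not certain, and the length serves a stated aim, equal numbers per clinician in both arms. This limits the risk but does not remove it.

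**Conclusion.** The point holds as a low-severity improvement. The article fixes one published block size within clinician in a trial that cannot be masked and has self-reported primary outcomes. If allocation is sequential and someone keeps a count, 11.1% of allocations are certain and 62.8% can be guessed. Under the assumed shift of 0.1 to 0.25 SD at the certain places only, the SCL-90 bias would be about 1.0 to 2.5 points before baseline adjustment, and any correlation with baseline that captures the selection would shrink it. Selective enrolment is possible, not demonstrated. The randomisation section contains no contradiction or error of arithmetic on this point; a safer rule is available at little cost.

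**What to change.** **Preferred.** In Recruitment and randomization, replace the block sentence with wording such as: *Within each clinician, consenting women are collected into a batch of 16, 20 or 24. After the last woman of the batch has consented, the whole batch is randomised 1:1 at once.* This yields 8, 10 or 12 women per GMC, inside the stated 8-12, and keeps the balance within clinician. If blocks of 16 were already meant to be allocated together, saying so settles the matter.

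**If allocation must be sequential.** Use block sizes varying at random among 16, 20 and 24 within clinician, not disclosed to those who recruit. This brings certain allocations from 11.1% to about 1-3%. Since correct guessing stays near 61%, it is the weaker choice.

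**Cost.** A short amendment and a change in how the list is produced; no extra patients or visits. With batches, a woman learns her visit type only when her batch is complete, although a GMC cannot be held until its group is assembled anyway. Someone outside recruitment should run the allocation, which is a small task but not nil. With varying blocks, the last block per clinician may be incomplete and GMC sizes will vary.

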### Power calculations

The primary aim of GMCs is to increase patient empowerment and to prevent an increase of psychological distress. Data on these outcome measures for *BRCA *mutation carriers are not yet available, therefore data from a rather comparable population, breast cancer patients, is used for the power analysis. Also, data of the SCL-90 is more widespread compared to empowerment data for breast cancer patients, therefore results of this questionnaire have been used. A healthy score on the SCL-90 ranges between 90-130, while breast cancer patients, one year or longer after curative treatment for breast cancer, achieved an average score of 138.5 [58]. In this study we strive for a high normal average score of 125. This implies that an average difference of 13.5 points can be defined as clinically relevant. The standard deviation is 45, which is based on three norm groups [49]. To assess a clinically relevant effect of GMC on psychological distress with a power of 80%, a two-side significance of 5%, a standard deviation of 45 and an expected drop-out of 15%, 80 patients need to be included in each group.

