### Statistical analysis

For the primary analysis a covariance analysis (ANCOVA) will be conducted. Differences in empowerment and SCL-90 scores (primary outcome measures) at baseline and one week after the GMC between the intervention group and control group will be compared. In addition ANCOVA provides the opportunity to compare trends over time between the two groups. The SCL-90 scores at T1 or T2 will be included as dependent variables and the group (individual consult or GMC) as independent variable. Furthermore, the SCL-90 score at baseline will be a covariate. The analysis of the secondary outcome measures is a repeated measurement analysis (ANOVA or mixed model) to compare trends over time between the two groups.

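### Randomisation is stratified by clinician, but the primary ANCOVA as written omits clinician; adding it is a small, nearly free improvement

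*Protocol article*

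**What the plan says.** Under Recruitment and randomization: "Randomization will take place per patient in a 1:1 ration and in blocks of 16 patients". The same paragraph explains that each clinician is to see equal numbers of patients in GMCs and in individual consultations, and "therefore we pre-stratified for clinician".

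Under Statistical analysis: "For the primary analysis a covariance analysis (ANCOVA) will be conducted". The model is then spelled out for one of the two primary outcomes: "The SCL-90 scores at T1 or T2 will be included as dependent variables", with "the group (individual consult or GMC) as independent variable", and "the SCL-90 score at baseline will be a covariate". Secondary outcomes are to be analysed with repeated-measures ANOVA or a mixed model comparing trends between groups. Clinician is mentioned in none of these analyses.

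**The concern.** Blocking within clinician keeps the two arms balanced on clinician, so differences between clinicians largely cancel out of the treatment contrast. A model without clinician leaves those differences in the residual. It then reports a standard error for a design in which clinician was free to vary between arms, which is not the design used.

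At stake is a mismatch between reported and actual precision: intervals slightly too wide and a test slightly less likely to reject than it could be. The estimate itself stays unbiased, because allocation is 1:1 within each clinician. The article fixes the dependent variable, factor and covariate of the model, so someone following it literally would fit the wrong model for the randomisation.

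**Working it through.** **Inputs from the article (Power calculations).** Difference 13.5 points ("This implies that an average difference of 13.5 points can be defined as clinically relevant"), SD 45, two-sided 5%, power 80%, drop-out 15%, 80 per group. Completers per arm: 80 × 0.85 = 68.

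**Assumptions.** The article gives neither the number of clinicians nor the variance between them. Let c be the share of the baseline-adjusted residual variance that lies between clinicians, taken as 0, 0.02, 0.05 and 0.10. The baseline–follow-up correlation r is not given either; 0.5 and 0.78 are shown.

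**The article's own figure.** n per arm = 2 × 45² × (1.960 + 0.842)² / 13.5² ≈ 174.4, so 175 evaluable, and 175/0.85 = 206 to recruit, not 80. With 68 per arm and no covariate, power is 41.7%. The figure of 80 is approached with an ANCOVA if r is about 0.78, which is not stated; this is why 0.78 is included. The shortfall is a separate point. Only the 68 completers are carried forward.

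**Effect of omitting clinician, ignoring correlation within sessions.**

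- Residual SD after baseline: S = 45 × √(1 − r²).
- SE reported without clinician: S × √(2/68).
- Actual SE under stratified allocation: S × √(1 − c) × √(2/68).
- Ratio reported/actual: 1/√(1 − c).
- Actual type I error: 2 × [1 − Φ(1.96/√(1 − c))].
- Power without clinician: Φ((13.5 − 1.96 × reported SE)/actual SE). Power with clinician: Φ(13.5/actual SE − 1.96).

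Example, r = 0.5 and c = 0.10: S = 38.97; reported SE = 38.97 × 0.1715 = 6.68; actual SE = 6.68 × 0.9487 = 6.34; ratio 1.054.

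| c (assumed) | Reported SE too large by | Actual type I error without clinician | Power without / with clinician, r = 0.5 | Power without / with clinician, r = 0.78 |
|---|---|---|---|---|
| 0 | 0% | 0.050 | 52.4% / 52.4% | 79.8% / 79.8% |
| 0.02 | 1.0% | 0.048 | 52.4% / 53.2% | 80.1% / 80.6% |
| 0.05 | 2.6% | 0.044 | 52.5% / 54.5% | 80.4% / 81.8% |
| 0.10 | 5.4% | 0.039 | 52.5% / 56.7% | 81.1% / 83.8% |

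**Check by simulation** (160 patients, blocks of 16 within clinician, 15% drop-out, r = 0.5, c = 0.10, no session effect). With 5 clinicians, the average model SE without clinician is 6.63 against an empirical 6.44; with clinician it is 6.37 against 6.41. The model SE falls by a factor 6.63/6.37 = 1.04. With 2 clinicians the figures are 6.53 against 6.33, and 6.35 against 6.30; the factor is 6.53/6.35 = 1.03. The simulated gap is a little smaller than the formula gives, because a handful of sampled clinicians shows less than the full assumed variance.

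**Adding correlation within GMC sessions.** If one block fills one session, 16/2 = 8 women sit together, of whom 8 × 0.85 = 6.8 complete. For an assumed within-session correlation of 0.05, the variance of the GMC-arm mean is multiplied by 1 + 5.8 × 0.05 = 1.29. The control arm is unaffected, so the variance of the difference rises by (1.29 + 1)/2 = 1.145 and the actual SE by √1.145 = 1.07. That outweighs the largest clinician effect in the table and works in the opposite direction. Simulated type I error, without and with clinician (5 clinicians, c = 0.10):

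- no session correlation: about 0.045 and 0.052;
- session correlation 0.05: about 0.060 and 0.066.

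**The case against.** The strongest reply is that a journal article only sketches the model. It names a covariate for the SCL-90 and none for empowerment, never says the list is complete, and may leave stratification terms to a fuller plan. That is a fair reason to treat the point as minor. It does not remove it: factor and covariate are stated for the SCL-90 model, and the stated randomisation stratum is not among them.

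Three further objections stand, and they limit what may be claimed.

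- **Reason for stratifying.** A reader might infer that the design stratified because clinicians were expected to influence outcome. The article gives a different reason: equal numbers of GMC and individual patients per clinician. Nothing in it says that clinicians differ on distress or empowerment.
- **Direction.** A reader might infer that the stated test is simply conservative. That holds only if clinicians differ and women in the same session are uncorrelated. With a modest assumed session correlation the error rate passes 5%, and adding clinician alone moves it slightly further up.
- **Size.** The shares of 2%, 5% and 10% are assumptions. In a single centre, with one visit and adjustment for baseline, the true share could be near zero.

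**Conclusion.** The point holds as a minor one: the article stratifies by clinician and writes a primary model without clinician. If clinicians explain an assumed 2% to 10% of residual variance, and leaving session correlation aside, the reported standard error is about 1% to 5% too large and roughly 1 to 4 points of power are given up. With no clinician differences the loss is nil. The effect estimate is unbiased in either case.

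It would be tempting to say that the omission wastes patients the trial cannot spare. The documents do not support that: no between-clinician variance is given, the balance within clinician is already secured by the randomisation, and the gap between 206 and 80 per arm is far larger than anything this change could recover.

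**What to change.** State in Statistical analysis that clinician, as used to stratify randomisation, enters as a fixed effect in the ANCOVA for both empowerment and SCL-90, and in the repeated-measures models for the secondary outcomes.

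The cost is one phrase and one degree of freedom fewer than the number of clinicians. With 136 completers (2 × 68) and, say, 5 clinicians, residual degrees of freedom go from 136 − 3 = 133 to 129. In the simulation with no clinician differences, the average SE rose only from 6.703 to 6.721, about 0.3%.

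Correlation within GMC sessions needs its own decision in the analysis plan. The clinician term should not be presented as dealing with it, nor as a remedy for the sample size.
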